**Methods:**

The study has a two-armed cluster randomized design in which the participating rehabilitation coordinators are randomized into delivering the intervention or providing care-as-usual. Employees on sick leave due to common mental disorders will be recruited by an independent research assistant. The intervention aims to improve the employee’s return-to-work process by identifying problems perceived as hindering return-to-work and finding solutions. The rehabilitation coordinator facilitates a participatory approach, in which the employee and the employer together identify obstacles and solutions in relation to the work situation. The primary outcome is total number of sick leave days during the 18-month follow-up after inclusion. A long-term follow-up at 36 months is planned. Secondary outcomes are short-term sick leave (min. 2 weeks and max. 12 weeks), psychological symptoms, work ability, presenteeism and health related quality of life assessed at baseline, 6 and 12-month follow-up. Intervention fidelity, reach, dose delivered and dose received will be examined in a process evaluation. An economic evaluation will put health-related quality of life and sick leave in relation to costs from the perspectives of society and health care services. A parallel ethical evaluation will focus on the interventions consequences for patient autonomy, privacy, equality, fairness and professional ethos and integrity.

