Previous studies have shown that problem-solving skills and work-focused cognitive behavioral therapy are more effective than guideline-based interventions in reducing the time to first RTW among employees on sick-leave for CMDs. Guideline-based interventions did not reduce time to return to full-time work [7, 14, 18, 19]. In a web-based intervention which included problem-solving skills and relapse prevention, a significantly faster first RTW was found for the intervention group. No significant differences were found for time until full RTW or in reduced total number of days on sick leave at the 12-month follow-up [20]. A review of interventions to improve time to first RTW among people with depression gave moderately good evidence that workplace interventions in combination with clinical interventions reduced the number of days on sick leave significantly more than clinical interventions alone [21]. Similar results were found by an updated review which evaluated the effects of workplace interventions among workers with mental health problems. The results demonstrated a significantly better reduction in time to first RTW than care-as-usual [15]. A cluster-randomized controlled trial in the Netherlands demonstrated the 12-month effectiveness of a problem-solving intervention for reducing recurrent sick leave among workers with CMDs. The intervention group had a lower incidence of recurrent sick leave than the control group which received care-as-usual [11]. Economic evaluations of such interventions have shown varying results, from reduced to increased health care costs [22–25].

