### Primary outcome

#### Registered sick leave

The primary outcome is the total number of days of sick leave 18 months after baseline. Data from MiDAS will be collected from baseline until the 18-month follow-up and for the 24 months before baseline. Information about the number of days on sick leave, episodes of sick leave after RTW, and receipt of disability pension will be collected for all participants. Sickness benefit and disability pension will be analyzed separately.

The total number of days of registered sick leave will be calculated after 36 months in the same way as at the 18-month follow-up.

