##### Part-time registered sick leave

Part-time registered sick leave will be calculated from baseline during the 18-month follow-up as registered part-time (25/50/75% of full-time) sickness absenteeism.

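### Analysing disability pension apart from sickness benefit lets a move to a pension lower the primary sick-leave total at 18 months, and again at 36 months

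*Protocol article*

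**What the plan says.** The Registered sick leave section of the protocol article defines the endpoint: "The primary outcome is the total number of days of sick leave 18 months after baseline". The abstract agrees: "The primary outcome is total number of sick leave days during the 18-month follow-up after inclusion". The days come from the social insurance register. The section also lists what will be extracted, including "episodes of sick leave after RTW, and receipt of disability pension will be collected for all participants", and then fixes how the two benefits relate: "Sickness benefit and disability pension will be analyzed separately".

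It gives no rule for the days after a pension starts. It carries the definition forward to the long-term follow-up: "The total number of days of registered sick leave will be calculated after 36 months in the same way".

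Degree of leave appears in a separate secondary outcome, defined as "registered part-time (25/50/75% of full-time) sickness absenteeism". The article does not say whether a part-time day enters the primary total as a whole day or by its degree.

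**The concern.** The trial asks whether the intervention helps people return to work, and its hypothesis is fewer sick leave days. For that question, a day on disability pension and a day on sickness benefit are both days lost to work. If only the benefit days are counted, the count ends when a pension begins, just as it ends when the person goes back to work. The primary endpoint then cannot tell the least favourable work outcome from the most favourable one after that date.

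If pensions are granted unequally between the arms, the arm with more of them gains an apparent reduction in sick leave. The cost-effectiveness analysis also takes change in sick leave days as its effect, so it would inherit the problem if it uses the same count. The exposure is greater at 36 months, where there is more time for pensions to start and more follow-up for each one to remove.

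**Working it through.** The article has no figure to reproduce on this point. It states no pension rate, mean number of days or standard deviation. What follows is arithmetic on stated assumptions.

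**Inputs**
- Follow-up window: 18 months, taken as 548 days; 36 months as 2 × 548 = 1,096 days.
- Planned size: 110 participants per arm (Statistical power section).
- Target: a 20% difference in registered sickness absence (same section), read here as relative; the article does not give the scale.
- Assumed: the move is from full benefit to full pension, at day 270 or day 365, and the person would otherwise have stayed on benefit to the end of the window.
- Assumed: an excess of 1%, 2% or 5% of one arm makes this move (110 × 0.01 = 1.1 people to 110 × 0.05 = 5.5 people).
- Assumed for scale: a control mean of 150 days, so 20% is 30 days.

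**Step 1: one person, three courses after day 270**

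| Course | Benefit days only | Benefit or pension days |
|---|---|---|
| Full return to work at day 270 | 270 | 270 |
| Pension from day 270 | 270 | 548 |
| Benefit to day 548 | 548 | 548 |

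Under the separate count, the pension ties with full return and scores 548 − 270 = 278 days better than staying on benefit. With a pension from day 365 the gap is 548 − 365 = 183 days.

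**Step 2: effect on the arm mean at 18 months**

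Shift = excess share × uncounted days.

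| Excess | Pension from day 365 | Pension from day 270 | Share of a 30-day effect |
|---|---|---|---|
| 1% | 0.01 × 183 = 1.8 days | 0.01 × 278 = 2.8 days | 6–9% |
| 2% | 0.02 × 183 = 3.7 days | 0.02 × 278 = 5.6 days | 12–19% |
| 5% | 0.05 × 183 = 9.2 days | 0.05 × 278 = 13.9 days | 31–46% |

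The range is therefore about 2–14 days. Over assumed control means of 100 to 250 days, the share of a 20% effect runs from 1.8/50 = about 4% to 13.9/20 = about 70%.

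**Step 3: 36 months**

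A pension that starts at day 548 does not touch the 18-month count, but it leaves 1,096 − 548 = 548 days uncounted at 36 months. An excess of 1% gives 0.01 × 548 = 5.5 days and an excess of 5% gives 0.05 × 548 = 27.4 days, under the same assumption of continued full leave.

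**Step 4: no imbalance**

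If the arms have the same pension share and timing, both means fall by the same amount and the difference in days is unchanged.

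**The case against.** The strongest reply is that the effect is probably small. Participants are employed, aged 18–59, on leave for 2 to 12 weeks with mild to moderate disorders, and severe disorders are excluded. Nothing in the article shows that pensions within 18 months will be frequent, let alone unequal between arms. The upper figures need an excess of five or six people in one arm of 110, each of whom would have stayed fully on leave for all the remaining days.

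Nor is a pension case a low score in absolute terms. Someone on benefit until month 9 has already accrued 548/2 = 274 days, which is 124 more than an assumed mean of 150. Replacing 3% of average participants with such cases would raise the arm mean by 0.03 × 124 = 3.7 days. Keeping two different benefits apart is also a declared choice, and because pension receipt is collected for everyone and analysed, an imbalance would be seen.

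Much of this stands, and it limits the size. It does not remove the point. The relevant comparison is with the same person's course had no pension been granted, and against that the count is too low. Seeing an imbalance in a separate analysis does not correct the primary contrast, and the article names no analysis that does.

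A reader might go further and infer that partial return to work scores as no change, because the total is a plain number of days and degree of leave sits in a secondary outcome. The article does not support this. No section says that part-time days count as whole days, and this is a counting detail that an article may leave to the full plan. Partial return is measured elsewhere: time to partial and to full return and the prevalence of partial leave under the self-reported outcomes, and registered part-time leave as its own outcome. The Background does report one web-based trial in which "No significant differences were found for time until full RTW or in reduced total number of days on sick leave", but it speaks of first return and never of partial return, and it also cites a review in which days on sick leave did fall.

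**Conclusion.** The point holds for disability pension. As stated, the primary count stops when a pension starts, so a lasting exit from work lowers the total relative to remaining on benefit and cannot be told from a return to work. The rule is repeated at 36 months, where the exposure is greater.

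The size cannot be established from the article. Under an excess of 1–5% in one arm, moving at day 270–365 and otherwise on full benefit to day 548, the bias in that arm's mean is about 2–14 days. It is near zero if pensions are rare or balanced, which may well be the case in this population at 18 months. This is a worthwhile correction to the endpoint definition, and it does not by itself put the trial's conclusion in doubt. On degree of leave, the article leaves the rule open; that is something to state, not an error shown.

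**What to change.** Before outcome data are seen, define a combined count: every day from baseline to 18 months on which the participant receives sickness benefit or disability pension. Use it as the primary count, or at least as a prespecified analysis reported beside the primary one. Keep sickness benefit alone as the other analysis, and apply the same definition at 36 months.

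Say in the same sentence whether part-time days count whole or by degree, and count a day with both a partial benefit and a partial pension once (or by the sum of degrees, up to one full day).

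Pension receipt is already to be collected for all participants; confirm that the register extract includes its start date and degree. The remaining cost is wording, one further analysis, and somewhat less direct comparability with published counts of sickness-benefit days, which the benefit-only analysis preserves.

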#### Secondary outcomes

Self-reported short-term sick leave, part-time registered sick leave, psychological symptoms, work ability, impairment of work performance, presenteeism, health-related quality of life (HRQoL).

##### Self-reported sick leave and return to work

Short-term sick leave will be assessed by the question: ‘How many days in the past four weeks have you been absent from work because of illness? Answer with a number between 0 and 28 days’. Self-reported, short-term sick leave has been shown to demonstrate acceptable reliability [31]. The time from baseline until 1) partial RTW or 2) full RTW (defined as working ordinary hours for an uninterrupted period of at least four weeks) will be calculated. The prevalence of no sick leave, partial and full-time sick leave during the 12-month follow-up will be calculated.

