### Measurements and procedure

Data will be collected by questionnaires, text messages and the use of registers. Register data will be collected from the Micro Data for the Analysis of Social Insurance register (MiDAS) from the Social Insurance Agency, the Västra Götaland region’s Vega register which is the patient register for Region Västra Götaland, and the Longitudinal Integration Database for Health Insurance and Labor Market Studies (LISA), administrated by Statistics Sweden. Web-based questionnaires will be administered at baseline and after 6 and 12 months. Text messages will also be sent to the employees every fourth week over a 12-month period. The use of text messages enables us to measure short-term sick leave (≤ 14 days) that is not covered by the MiDAS register. A 36-month follow-up of sickness absenteeism based on register data is planned.

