### Economic evaluation

A cost-utility analysis will be conducted to analyze changes in HRQoL measured by EQ-5D and translated using the Swedish experience-based value set [39] and societal costs. Direct costs for health care will be estimated based on administrative data from the Vega register. Indirect costs will be estimated using the human capital approach from sick leave (self-reported and registered in MiDAS) and self-reported presenteeism. All-cause health care use will be collected from the Vega register over 18 months after baseline. This register covers diagnoses, the reason for visits and measures taken for patients visiting primary and specialized healthcare in the Västra Götaland region of Sweden [47].

Moreover, a cost-effectiveness analysis will be conducted to compare changes in days on sick leave to the direct health care costs, including the costs for conducting the intervention, calculated based on time reported by the RCs.

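### Self-reported short-term sick leave has two conflicting definitions, and the four-week item meets neither because it also counts registered days

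*Protocol article*

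**What the plan says.** All references are to the protocol article.

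- **Abstract, Methods:** the secondary outcomes include "short-term sick leave (min. 2 weeks and max. 12 weeks".
- **Measurements and procedure:** "The use of text messages enables us to measure short-term sick leave (≤ 14 days) that is not covered by the MiDAS register". On timing: "Text messages will also be sent to the employees every fourth week over a 12-month period".
- **Secondary outcomes:** self-reported short-term sick leave is a named outcome.
- **Self-reported sick leave and return to work:** "Short-term sick leave will be assessed by the question" that follows, namely "How many days in the past four weeks have you been absent from work because of illness", with the instruction "Answer with a number between 0 and 28 days".
- **Recruitment of participants and Inclusion criteria:** entry requires a current sick leave period of 2 to 12 weeks.
- **Methodological considerations:** the employer usually pays up to and including day 14, so MiDAS data start at day 15 of a spell.
- **Economic evaluation:** "Indirect costs will be estimated using the human capital approach from sick leave (self-reported and registered in MiDAS", together with self-reported presenteeism. No rule is given for days that appear in both sources.

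**The concern.** The abstract and the procedures section cannot both describe this outcome. As spell lengths, 2 to 12 weeks and at most 14 days meet only at exactly 14 days. The abstract's range is the same as the eligibility window.

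The item fits neither definition. It places no limit on the length of the spell and does not ask respondents to leave out days paid by the Social Insurance Agency. In this population that matters from the start of follow-up, because participants join during a spell that is, or soon will be, in the register. Ongoing registered leave would then be scored as short-term leave. A between-arm difference in the secondary outcome could reflect the length of the index spell rather than the employer-paid absence that the item was introduced to capture.

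The same overlap bears on the economic evaluation. If the self-reported days are taken to be what MiDAS lacks, as the procedures section describes them, they could be added to MiDAS days that they already contain.

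**Working it through.** The plan gives no figure that depends on this point, so there is none to reproduce. The check is a day count.

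**Inputs.** The recall window is 28 days and the item counts all absent days in it (Self-reported sick leave and return to work). Registration starts at spell day 15 (Methodological considerations). Assumptions: full-time absence, accurate recall, and answers in calendar days.

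**Formulas**, for one window:

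- S = all absent days in the window (what the item asks for)
- R = absent days in the window with spell day 15 or later (what MiDAS holds)
- U = S − R (unregistered days)
- Unadjusted sum = S + R

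| Full-time spell and window | S | R | U | S + R |
|---|---|---|---|---|
| New 7-day spell | 7 | 0 | 7 | 7 |
| New 14-day spell | 14 | 0 | 14 | 14 |
| New 21-day spell | 21 | 7 | 14 | 28 |
| New 28-day spell | 28 | 14 | 14 | 42 |
| 84-day spell, window from day 15 | 28 | 28 | 0 | 56 |
| 84-day spell, window from day 29 | 28 | 28 | 0 | 56 |

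**Label.** Up to 14 days, S = U and the item does what the procedures section says. Beyond that, S exceeds U by R. In the last two rows the item reads 28 where the days outside MiDAS number 0. These rows are the situation of a participant who is past day 14 at baseline and still on full-time leave four weeks later.

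**Costs, only if the sources were added without adjustment.** True absence is S, so the excess is R. That is 42 instead of 28 days for a new 28-day spell (14/28 = 50%) and at most 56 instead of 28 (100%). If respondents counted working days instead (assumed 5 in 7), a full window would give S = 20, so 20 + 28 = 48 against 28 (20/28 = 71%). Spells of 14 days or less are not inflated. Text messages run for 12 months and MiDAS follow-up for 18, so registered days in months 13 to 18 cannot be doubled.

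**The case against.** **Double counting is not stated.** A reader might infer that the economic evaluation counts registered days twice. The article does not support that. It names two sources and does not say they are summed. The procedures and the methodological discussion both present self-report as filling the gap that MiDAS leaves, and an overlap rule is the sort of detail a journal article can leave to a fuller plan. This objection stands: double counting is a risk, and the missing rule is not a fault in itself.

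**The wider question has a use.** The same section also plans time to partial and full return to work and the prevalence of no, partial and full-time leave, for which total absence is relevant. Registered days are collected for all participants, so unregistered days can be recovered by linkage. This also stands. The measurement is not lost; its label and derivation are wrong.

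**The 0 to 28 range proves nothing alone.** Two short spells could exceed 14 days in total. True, but the point rests on the absence of any spell limit or exclusion of registered days.

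**The mode of the item is not stated.** Its section does not call it a text message. The link is an inference from the four-weekly text messages, the matching recall period and the shared construct.

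**It does not simply duplicate the primary outcome.** A reader might infer that it does. The two overlap during registered spells, but they differ in horizon (12 against 18 months) and in coverage of the first 14 days of a spell, and the documents give no data to measure their agreement.

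None of this removes the conflict between the two printed definitions, or between both of them and the printed item. A later analysis plan could add a rule, but the published definitions would still need correcting.

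**Conclusion.** The point holds for the definition of the secondary outcome. The article gives two incompatible meanings of short-term sick leave, and the item assigned to it measures total self-reported absence. For a full-time spell, the error in one window ranges from 0 (spells of 14 days or less) to 28 days (windows wholly after day 14).

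For the economic evaluation the conclusion is conditional. If the two sources were added unadjusted, which the article does not state, registered days within the 12 text-message months could be counted twice. The 50% and 100% excesses are for single windows. They are not estimates for the trial, because the documents do not give the distribution of spell lengths or the share of part-time leave.

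The sizes assume full-time leave, accurate recall and calendar-day answers. The primary outcome comes from MiDAS alone and is unaffected. The change should be made, since it is cheap and the outcome cannot be interpreted as now described.

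**What to change.** 1. Correct the abstract so that it no longer gives 2 to 12 weeks, and use one definition throughout.
2. Report the item under its own name, as total self-reported absence in the past four weeks.
3. Derive a second measure by linking each 28-day window to MiDAS dates and removing days already registered. Call it unregistered days, not short-term spells: a single 28-day spell leaves 14 such days, so the measure includes the first 14 days of longer spells.
4. State how part-time registered leave (25, 50 or 75%) enters the subtraction, and whether answers are calendar or working days. Say how negative residuals are handled; setting them to zero keeps positive recall errors, drops negative ones, and so biases the result upward.
5. In the economic evaluation, state that each calendar day is costed once: MiDAS days plus only the unregistered self-reported days.

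The cost is a change of wording and one linkage step on data already planned for collection, assuming that MiDAS spell dates are supplied. Some recall error will remain in the residual.

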##### Part-time registered sick leave

Part-time registered sick leave will be calculated from baseline during the 18-month follow-up as registered part-time (25/50/75% of full-time) sickness absenteeism.

##### Psychological symptoms

Reduction of self-reported anxiety and depression will be measured by the Hospital Anxiety and Depression Scale, a well-established and much used scale in primary health care with 14 items used for the assessment of anxiety (7 items) and depression (7 items) [32]. The response format is a 4-point Likert scale, ranging from 0 to 3, with higher scores indicating anxiety and/or depression. Self-reported, stress-related exhaustion disorder will be assessed by means of the self-reported exhaustion scale (s-ED), a scale which has demonstrated construct and predictive validity. The response format is yes/no [33].

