##### Work ability

Work ability will be measured as improved working ability and reduction in work-related stress. The measure is self-reported work ability assessed by three items from the Work Ability Index. The items concern perceived work ability in relation to physical and mental demands at work and the employee’s prognosis of his/her work ability two years hence [34].

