##### Health problems

HRQoL will be assessed by the EuroQoL health state questionnaire (EQ-5D). The response format is a 3-level scale, with higher levels indicating severity [39]. We will use the subscale for insomnia from the Karolinska Sleep Questionnaire, to assess sleeping problems. The response format range from 0 (never) to 5 (always), higher scores indicate severity [40].

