#### Data analysis

Statistical analyses adapted for cluster-randomized controlled trials will be conducted. Linear and generalized linear models will be used. Intention-to-treat analyses and, if relevant, per-protocol analyses will be conducted. Potential confounders will be adjusted for in the analyses, if they prove to be unevenly distributed and might be expected to have an impact on the outcomes when the intervention is compared with the control condition. Possible interaction effects on the primary and secondary outcomes for (1) gender x treatment, and (2) number of sessions with RC x treatment will be assessed. If they are statistically significant, appropriate analyses will be considered. Data collected from interviews and focus groups will be analyzed by methods adapted for qualitative data and normative analysis (cf. [48, 52, 53]).

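### Baseline scores of the questionnaire outcomes enter the analysis only if the arms look uneven; including each outcome's own baseline value in every case would be a free gain in precision

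*Protocol article*

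**What the plan says.** Three places in the protocol article use the language of change:

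- Psychological symptoms: "Reduction of self-reported anxiety and depression will be measured by the Hospital Anxiety and Depression Scale".
- Work ability: "Work ability will be measured as improved working ability and reduction in work-related stress". The next sentence names the instrument: "The measure is self-reported work ability assessed by three items from the Work Ability Index".
- Economic evaluation: "A cost-utility analysis will be conducted to analyze changes in HRQoL measured by EQ-5D".

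Other questionnaire outcomes are worded neutrally. As a secondary outcome, quality of life is simply a level: "HRQoL will be assessed by the EuroQoL health state questionnaire (EQ-5D"). The work-impairment and insomnia scores carry no change wording, and neither does the exhaustion scale ("The response format is yes/no").

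Baseline values will exist. The abstract's Methods paragraph lists the secondary outcomes, ending with "health related quality of life assessed at baseline, 6 and 12-month follow-up", and the Measurements and procedure section puts the web questionnaires at the same three times.

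On the model, the Data analysis section says "Linear and generalized linear models will be used", with methods suited to cluster randomisation. It then makes adjustment depend on two conditions: the variable must prove uneven between the arms, and it must plausibly influence the outcome. No other covariate rule appears, and no section says that a questionnaire outcome is adjusted for its own baseline score.

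**The concern.** A baseline score on the same instrument is usually among the strongest predictors of the follow-up score. Its main value in the model is precision, and that gain is there whether or not the arms differ at baseline. A rule that admits it only after an imbalance is seen discards the gain in the balanced case. It also makes the final model depend on the data.

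At stake are the comparisons of HADS anxiety and depression, work ability, work impairment, insomnia and EQ-5D, and the utility side of the cost-utility analysis. Intervals would be wider than necessary, so real effects would be easier to miss. A modest chance difference at baseline, too small to be called uneven, would pass into the estimate. The primary outcome, registered sick-leave days, is outside this point.

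**Working it through.** **Inputs from the protocol article (Statistical power):** 220 participants, 110 per arm; 10 clusters of 11 per arm; intra-cluster correlation 0.010; alpha 0.05 (two-sided assumed).

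**Inputs assumed, because the article gives none:** the correlation ρ between baseline and follow-up score; equal variances at both times, set to 1; for the power illustration, a true effect of 0.35 SD. The intra-cluster correlation was set for the sick-leave outcome and is borrowed here. The formulas apply to scores treated as continuous, not to the yes/no exhaustion scale.

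**The plan's own figure.** The article states around 80% power for a 20% difference in registered sickness absence. It gives no mean, SD or rate, so this cannot be strictly reproduced. It concerns the primary outcome, and no power is claimed for the questionnaire outcomes. Nothing below contradicts it.

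**Step 1: variance under each analysis.**

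- Change from baseline, unadjusted: 2(1 − ρ)
- Follow-up score, unadjusted: 1
- Either one with baseline as a covariate: 1 − ρ²

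Relative to the baseline-adjusted analysis, the ratios are 2(1 − ρ)/(1 − ρ²) = 2/(1 + ρ) for change and 1/(1 − ρ²) for follow-up.

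| ρ (assumed) | change: 2/(1+ρ) | follow-up: 1/(1−ρ²) |
|---|---|---|
| 0.3 | 2/1.3 = 1.54 | 1/0.91 = 1.10 |
| 0.5 | 2/1.5 = 1.33 | 1/0.75 = 1.33 |
| 0.6 | 2/1.6 = 1.25 | 1/0.64 = 1.56 |
| 0.7 | 2/1.7 = 1.18 | 1/0.51 = 1.96 |
| 0.8 | 2/1.8 = 1.11 | 1/0.36 = 2.78 |

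Both ratios exceed 1 throughout. They move in opposite directions: the loss with change scores shrinks as ρ rises, while the loss with follow-up scores grows.

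**Step 2: what this does to power.** Design effect = 1 + (11 − 1) × 0.010 = 1.10. Standard error = √(4 × v × 1.10/220), with v from step 1; power from the t distribution with 20 − 2 = 18 degrees of freedom.

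| ρ | change, unadjusted | follow-up, unadjusted | baseline-adjusted |
|---|---|---|---|
| 0.3 | SE 0.167, power 0.51 | SE 0.141, power 0.65 | SE 0.135, power 0.69 |
| 0.5 | SE 0.141, power 0.65 | SE 0.141, power 0.65 | SE 0.122, power 0.77 |
| 0.6 | SE 0.126, power 0.74 | SE 0.141, power 0.65 | SE 0.113, power 0.83 |
| 0.7 | SE 0.110, power 0.86 | SE 0.141, power 0.65 | SE 0.101, power 0.91 |

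**Step 3: chance imbalance left in the estimate.** The SD of the baseline difference between arms is √(4 × 1.10/220) = 0.141 SD. A difference of that size is ordinary and could easily be judged balanced. Unadjusted, it moves the change-score estimate against the imbalance by (1 − ρ) × 0.141 = 0.10, 0.07 or 0.06 SD at ρ = 0.3, 0.5, 0.6. It moves the follow-up estimate with the imbalance by ρ × 0.141 = 0.04, 0.07 or 0.08 SD. Including the baseline value removes either shift.

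**The case against.** A reader might infer that the plan sets these outcomes up as raw change from baseline in place of a baseline-adjusted score. The text does not support that. 'Reduction' and 'improved' can simply name the hoped-for direction, and no section defines a difference variable. The model sentence does not name the dependent variable or exclude baseline as a covariate. A change-score model that includes baseline gives the same treatment effect as a baseline-adjusted follow-up analysis. For EQ-5D the change wording is confined to the economic evaluation. That section also speaks of changes in sick-leave days, which the Primary outcome section defines as a total over follow-up, so the word may mean no more than a difference between arms. All of this stands.

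A second objection is that a journal article may leave covariate lists to an analysis plan that is not shown. That would settle the matter if the article were silent. It is not: it states a rule for when covariates enter, and a baseline score in apparently balanced arms fails that rule.

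Third, a clearly imbalanced baseline score could be picked up by the rule, and an unadjusted comparison is unbiased over repeated randomisations. Both are true. They limit the point to lost precision, and to the shift from imbalances too small to trigger adjustment. Finally, the size depends on assumed correlations: with change scores and ρ = 0.8 the variance excess is only 11%.

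**Conclusion.** The point holds as a free improvement, limited to the secondary questionnaire outcomes and the utility side of the economic evaluation. The stated adjustment rule leaves out each outcome's own baseline score when the arms look balanced. That costs precision whichever of change or follow-up is compared: at assumed correlations of 0.3 to 0.6, a variance 1.25 to 1.54 times larger for change and 1.10 to 1.56 times larger for follow-up scores.

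The power figures are illustrations. They rest on an assumed correlation, an assumed 0.35 SD effect and an intra-cluster correlation chosen for another outcome. The plan makes no wrong numerical statement here and does not commit itself to an unadjusted change score. For the work-impairment and insomnia scores, which have no change wording, the point rests on the adjustment rule alone.

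**What to change.** In the Data analysis section, state that for each questionnaire outcome (HADS anxiety, HADS depression, the work-ability items, the impairment and insomnia scores, and the EQ-5D index) the 6- and 12-month values are analysed in the clustered model with the same instrument's baseline value always included as a covariate, regardless of observed balance. In the Economic evaluation section, state that the between-arm utility (QALY) difference is adjusted for baseline EQ-5D. Reword the reduction, improvement and change phrases so that they name the measured score.

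The cost is analysis wording only. The baseline questionnaire is already planned, so no extra participants, visits or items are needed. In a model with about 20 clusters, one continuous baseline covariate per outcome is a small addition.
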